## Statistical analysis

3

Descriptive statistics will be used to report participants’ recruitment rate per month, proportion of participants enrolled from the total number screened, adherence rate and the drop-out rate. Specific criteria to determine the feasibility of this study will be a recruitment of two participants per month, the adherence rate of 85 %, and the drop-out rate of ≤20 %.

SPSS (version 28.0; IBM Corporation, Armonk, NY) will be used for statistical analysis. We will report mean and SD for continuous data (OMAS, SEFAS, SF-36, time to full weight bearing, time to return to work and pre-injury activities) and percentage or number for categorical data (total and individual complications).

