### Study setting

2.2

Participants will be recruited between February to December 2024 from Christchurch Hospital, a tertiary trauma centre in Christchurch, New Zealand. We anticipate the full RCT running at this centre, in addition to other secondary and tertiary hospitals in New Zealand.

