#### Primary outcome measures

2.6.1

We will assess recruitment rate, adherence rate, and drop-out rate. We will use an eligibility criteria log to screen participants eligibility. The recruitment rate will be calculated as the proportion of enrolled participants to screened participants and the number of enrolled participants per month. Adherence rate will be identified by the proportion of participants who followed the weight bearing status to all participants at their allocated arm. This will be assessed through participants interviews at the end of the study. Drop-out rate will be measured through the proportion of participants who withdraw from the study after randomisation to those who initially enrolled in the study.

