### Recruitment procedure

2.7

The research administrator ([name]) at the centre will make the first approach for screening and explaining the study to potential participants. Eligible participants who are interested in our study will be provided with the information sheet and encouraged to consult with their GPs, family and friends about the study. They will be given adequate time to consider participating in the study prior to their operation. Informed consent for study participation will be obtained prior to surgery. Retrospective data collected from Christchurch Hospital theatre records showed 291 ankle fractures (excluding those with syndesmosis fixation) were operated on during a 12-month period. On the assumption that 50% of these patients would meet the inclusion criteria and agree to participate in our study, we estimate completing recruitment within one year.

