### Sample size

2.10

The minimum clinically important difference for the OMAS was reported 10.5 at three months [24]. Considering the average standard deviation at 16 from prior studies, this gives a sample size of 50 per group for the main trial to achieve 90 % power at a two-sided alpha of 0.05. Given a 20 % drop-out, we will need 120 participants in total for the full trial. In order to minimise the sample size of the pilot and main trial combined, and considering the medium effect size of 0.66, it is recommended that 13 participants per group are recruited for the pilot study [31]. Given a drop-out rate of 20 %, we will need a total of 32 participants for the pilot trial. It is anticipated that these patients will carry over to participate in the ongoing full RCT, pending a successful pilot RCT, ethics approval and appropriate funding.

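### The recruitment criterion of two participants per month is inconsistent with the pilot's own size and window: it accepts 22 to 31 enrolled in 11 months when 32 are needed

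*Protocol article*

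**What the plan says.** The protocol article fixes three quantities in three places.

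- **Threshold** (section 3, Statistical analysis): "Specific criteria to determine the feasibility of this study will be a recruitment of two participants per month". Adherence of 85% and a ceiling on drop-out, "the drop-out rate of ≤20"%, stand beside it.
- **Window** (section 2.2, Study setting): "Participants will be recruited between February to December 2024 from Christchurch Hospital". Section 2.7 (Recruitment procedure) puts it slightly more loosely: "we estimate completing recruitment within one year".
- **Size** (section 2.10, Sample size): "Given a drop-out rate of 20 %, we will need a total of 32 participants for the pilot trial". It is built on this statement: "it is recommended that 13 participants per group are recruited for the pilot study".

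Section 2.6.1 makes recruitment rate a primary outcome, measured as the enrolled share of those screened and as "the number of enrolled participants per month". Only the monthly rate has a threshold. Section 2.7 also gives the planning basis: 291 operated fractures in 12 months, half of them assumed eligible and willing.

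The article does not connect the threshold to the target of 32 or to the window, and it has no separate criterion that the pilot reach its size.

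**The concern.** A feasibility criterion is defined by the results it accepts. If the accepted rate, multiplied by the length of the window, falls short of the planned number, the pilot can be reported as having met its recruitment criterion after failing to recruit the number it said it needed in the time it gave itself.

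The stake is how a primary outcome is interpreted. The aim of the pilot is to judge whether a full trial is feasible, and section 2.10 makes carry-over of pilot patients into that trial depend, among other things, on the pilot being successful. Section 6 recalls an earlier trial of immediate weight bearing that stopped partly because recruitment was slow, so slow recruitment is a risk the authors already recognise.

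**Working it through.** **Inputs, all from the protocol article**

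- Threshold: 2 per month (section 3)
- Window: February to December 2024, inclusive, 11 months (section 2.2); lenient reading, 12 months (section 2.7)
- Pilot size: 32, from 13 per group = 26 before drop-out (section 2.10)
- Tolerated drop-out: 20% (sections 2.10 and 3)
- Planning pool: 291 operations in 12 months, 50% assumed to enter (section 2.7)

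**Step 1. Reproduce the plan's figure.** 26 × 1.2 = 31.2, rounded up to an even total, is 32. The stated size reproduces. Dividing by 0.8 instead gives 32.5, so 33, or 34 with equal arms; the difference does not affect this point.

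**Step 2. Enrolment at exactly the threshold** (rate × months)

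| Window | Enrolled at 2 per month | Short of 32 | Left after 20% drop-out |
|---|---|---|---|
| 11 months | 2 × 11 = 22 | 10 (31%) | 22 × 0.8 = 17.6 |
| 12 months | 2 × 12 = 24 | 8 (25%) | 24 × 0.8 = 19.2 |

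Both totals are below the 26 wanted even before drop-out is taken off.

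**Step 3. Rate needed to fill the pilot** (size ÷ months)

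- 11 months: 32/11 = 2.91 per month
- 12 months: 32/12 = 2.67 per month
- Time needed at 2 per month: 32/2 = 16 months

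**Step 4. Totals that pass the criterion but miss the size.** Over 11 months, 22 enrolled is 22/11 = 2.00 per month and 31 enrolled is 31/11 = 2.82 per month. Every total from 22 to 31 passes and misses 32.

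**Step 5. Compare with the plan's forecast.** 291 × 0.5 = 145.5 per year; 145.5/12 = 12.1 per month. At that rate 32 places fill in 32/12.1 = 2.6 months. The threshold is 2/12.1 = 16% of the forecast, about one-sixth.

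**Step 6. Check a rounded-up threshold.** Three per month averaged over the full 11 months is 3 × 11 = 33 participants. A fully recruited pilot of 32 scores 2.91 and would fail it, so rounding the rate up to 3 over a fixed window is not a workable repair.

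**The case against.** **Two per month is a minimum and not the forecast.** This stands. A reader might infer that the pilot cannot fill, but the document does not support that: section 2.7 implies about 12 per month, far more than is needed. The shortfall in the working arises only if recruitment runs near the threshold. What remains is that the threshold would call such a result acceptable.

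**The criterion may be meant for the full trial.** The Introduction and section 2.2 foresee a multi-centre trial, and a per-centre minimum of two per month could be coherent for it. This also stands in part. But section 3 words the criteria as applying to this study, and the article gives no number of centres, no duration for the full trial and no reason for the figure of two. For the same reason, a reader should not divide the full trial's 120 participants by two per month to obtain a recruitment time: that assumes a single centre, which is not the plan.

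**The criterion does not decide continuation mechanically.** Section 4 leaves that decision to discussion among the investigators, and both the monthly rate and the enrolled share of those screened will be reported, so a shortfall would be visible. This is fair, and it lowers the severity. It does not reconcile the three figures.

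**Recruitment could simply be extended.** The article states no extension; sections 2.2 and 2.7 give a fixed period and an expectation of finishing within a year.

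**The detail may sit in an analysis plan that is not shown.** The threshold, the window and the size are all fixed in this article and do not agree with each other, so this is an inconsistency and not an omission.

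**Conclusion.** Wrong as written, and should be fixed. The recruitment threshold does not match the pilot's own size and window. At the threshold the pilot enrols 22 of 32 in the stated 11 months, or 24 of 32 under the lenient one-year reading; 11-month totals from 22 to 31 meet the criterion and miss the size. The threshold is also about one-sixth of the rate implied by the planning assumption, so it would pass even if that assumption proved badly wrong.

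The conclusion rests on stated figures and simple arithmetic. The only reading involved is counting February to December as 11 months, and it survives the 12-month alternative. It does not show that recruitment will be slow, nor that two per month would be wrong as a per-centre minimum for a multi-centre trial. The consequence is limited to how the pilot's recruitment result is labelled and to its timeline; no treatment comparison is biased.

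**What to change.** Choose one of two changes, before the recruitment result is known.

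1. **Replace the criterion** with 32 participants randomised within the stated recruitment window. Expressed as a rate, this is at least 2.9 per month (32/11), computed to the date recruitment closes, so that a pilot that fills early is not penalised. The count is the cleaner wording, because a rate alone could be met by a pilot that closed early without reaching 32. Counting at randomisation matters because consent is taken before surgery and allocation follows only once the surgeon confirms stable fixation.
2. **Keep two per month**, state that it is a per-centre minimum for the multi-centre trial, give the reason for it, and restate the pilot's recruitment window as 16 months in sections 2.2 and 2.7.

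The enrolled share of those screened should not be given a threshold borrowed from the 50% in section 2.7. That 50% is a share of operated fractures without syndesmosis fixation, whereas the outcome's denominator is screened participants.

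Cost: one changed criterion under the first option, or a few changed sentences under the second. Under the first, the pilot is somewhat more likely to miss its recruitment criterion; under the second, the stated timeline becomes longer.

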To the best of our knowledge, despite a range of research aiming to shed light on this issue, no large-scale high-quality study has adequately compared immediate weight bearing following ankle fixation to six weeks non-weight bearing. Smeeing, Houwert [9] conducted an RCT with 115 patients randomised to either group 1 (unprotected immediate weight bearing and immediate ankle motion (within 24 h)); group 2 (protected early weight bearing in a cast (within 10 days) and ankle immobilization); or group 3 (unprotected non-weight bearing and immobilization (for six weeks). The primary outcome of the study showed a higher functional score and shorter time to return to work in patients in the unprotected immediate weight bearing group compared with the protected early weight bearing and unprotected non-weight bearing groups. This study was limited by a relatively small sample size and allowed weight bearing while also allowing range of motion exercises, making the effects of the weight bearing portion of their protocol difficult to isolate.

**Aim:** To conduct a pilot trial recruiting 32 participants with ankle fractures requiring ORIF, to assess the effects of immediate versus delayed weight bearing in the short term. This pilot RCT will test the feasibility of a full RCT through estimating the recruitment rate, adherence rate and drop-out rates for six months following their operation. The follow-on study will be a large-scale and multi-centre RCT to test whether immediate weight bearing following ankle fixation results in improved patient reported outcomes and earlier return to work without an increase in complications compared with patients managed with six weeks of non-weight bearing. The pilot trial will allow us to build the capacity and skills within our institution to effectively lead a multi-centre RCT.

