### Eligibility criteria

2.3

Patients who are treated with open reduction internal fixation due to a unilateral ankle fractures will be sought for study enrolment. Stable fixation must be achieved by the operating surgeon. While subjective, this is likely to include criteria such as the patient having good quality bone, a good lag screw, and no significant unexpected comminution. Inclusion criteria will be skeletally mature patients (closed distal tibial physes) who are operated on due to closed ankle fractures. There is no upper age limit for inclusion. Fracture patterns will include isolated medial, lateral or posterior malleolus fractures, bimalleolar and trimalleolar fractures. Additionally, ankle fractures treated with an external fixator prior to definitive surgery will be included. These criteria were selected as no study has yet shown the association between the type of fractures and post-surgical outcomes (e.g., Quality of Life, Function scores, complications) [[19], [20], [21]], thus, if the other inclusion criteria are met, patients with different types of fracture will be included. Patients must be physically active (with or without walking aids) in the community before the injury and must speak English or have an interpreter available.

Exclusion criteria will include fractures where stability is still questionable following fixation, as deemed by the operating surgeon. Patients with active infection at the surgical site, any compound fracture, pathological fractures, Pilon fractures, or concurrent injuries that preclude adhering to the follow up protocol will be excluded. We will exclude participants who are unable to follow the protocol due to neurologic disorders (i.e., cognitive impairment, substance abuse, mental illness, intellectual disability, and dense peripheral neuropathy) or significant additional physical impairment (i.e. polytrauma patients with other limb, head or visceral injuries). Any fracture where syndesmosis stabilisation is required will be excluded as post-rehabilitation practices are more conservative with this type of fracture [22]. We will exclude patients whose follow up care will be provided outside of Christchurch Hospital.

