### Interventions

2.4

Patients will receive pre-operative ankle x-rays as their primary imaging modality. CT scans will be obtained if deemed necessary by the orthopaedic team for surgical planning. All patients will be treated by orthopaedic registrars, fellows or consultants according to their preferred techniques. After surgery, all included patients will be placed in a moonboot (also known as a walker boot, or CAM boot). The moonboot consists of a rigid outer shell providing structural support for the foot and ankle, and inner padding to reduce pressure points. They can be removed for monitoring of the wounds. It allows for weight bearing while restricting ankle movement. Patients will be instructed to keep their moonboots on at all times, and to keep their wounds dry. Patients in the IWB group will bear weight as tolerated within 24 h. They will be encouraged to stand or walk without using walking aids. It is envisaged that patients in the IWB group will self-limit the amount of weight they put through their ankle based on their pain tolerance and physical fitness. If necessary, walking aids (crutches, walking frames etc.) will be provided as determined by the treating doctors, nurses, physiotherapists and occupational therapists. Patients in the DWB group will use walking aids (crutches, walking frames etc.) for mobilising and remain non-weight bearing for six weeks prior to allowing weight bearings as tolerated.

At approximately two weeks post-surgery, all patients will have their wounds reviewed in the outpatient clinic. Patients will then have their wounds redressed and be placed back into their moonboot to further 4 weeks.

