#### Secondary outcome measures

2.6.2

The Olerud and Molander Ankle Score (OMAS) is a widely used validated patient questionnaire for ankle injuries which scores pain, stiffness, swelling, and various functional abilities from 0 to 100 with 0 representing total impairment, and 100 representing a perfect ankle. The OMAS has high reliability, and high structural validity for assessment of ankle injuries [23]. Minimal Clinical Importance Difference (MCID) is the smallest difference in a patient reported outcome measure that a patient can consider beneficial. The MCID for patients with ankle injuries who underwent ORIF was reported to range between 10.5 and 15.0 points (median 12.5) at three to six months follow-ups [24].

Other secondary outcomes will include a health quality of life survey using SF-36 health survey, and the Self-Reported Foot and Ankle Score (SEFAS). SEFAS is foot and ankle specific Patient Reported Outcome Measure (PROM) scored from 0 to 48, with a higher score indicating a more favourable outcome. It was identified with high content validity and high internal reliability (ICC = 0.93) with no ceiling and floor effect [25]. Time to return to work, time to full weight bearing without walking aids, and return to pre-injury activities will be obtained from patients’ logs in their periodic visits.

Possible post-operative complications will include total and individual complications including venous thromboembolism, wound complications (superficial, and deep wound infection, and wound dehiscence), loss of reduction, fracture malunion/mal-reduction, non-union and implant failure requiring revision surgery. Total complications will be calculated as the ratio of participant with any type of complications to all participants at 6 months post-surgery. Evidence of venous thromboembolism or wound complication will be documented as yes/no during hospitalisation and up to six weeks post-surgery from the patient's medical record. Superficial infection will be as defined by the National Library of Medicine, where infection is confined to the skin and subcutaneous tissues of the incision. Deep wound infection involves infection in the muscles and facial layers [26,27] requiring surgical debridement. Dehiscence of the wound will also be recorded and categorized as a deep wound complication.

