#### Follow-up time points

2.6.3

Patient reported outcomes and radiographs will be obtained at six weeks, three and six-months post-surgery. Complications reported by the orthopaedic team will be documented by the research assistants from patient's medical records. The study timeline for participants recruitment and follow-up visits is described in Table 1 and Fig. 1.

**Table 1 tbl1:** Study timeline.

Assessment	Preoperative	Postoperative	2 weeks	6 weeks	3 months	6 months
**X-ray**	x			x	x	x
**CT-scan**	x					
**Participants screening**	x					
**Informed consent**	x					
**Participants eligibility**		x				
**Allocation**		x				
**Medical history**	x	x				
**Clinic visits (Complication outcomes)**			x	x	x	x
**Research visits (Functional outcomes)**				x	x	x

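### Times to full weight bearing, return to work and pre-injury activities are summarised by mean and SD although they are censored at six months, which can bias the descriptive comparison between arms

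*Protocol article*

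**What the plan says.** The Statistical analysis section puts three questionnaire scores and three times into one class: "We will report mean and SD for continuous data (OMAS, SEFAS, SF-36, time to full weight bearing, time to return to work", with pre-injury activities closing the list. All six are to be reported by mean and SD.

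The Secondary outcome measures section defines the times: "Time to return to work, time to full weight bearing without walking aids, and return to pre-injury activities will be obtained from" patient logs at the periodic visits. It names return to pre-injury activities without calling it a time, whereas the Statistical analysis section lists it among the continuous times.

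The last planned contact is at six months: "Patient reported outcomes and radiographs will be obtained at six weeks, three and six-months post-surgery". The feasibility criteria accept drop-out of up to 20%. Eligibility does not require employment, and "There is no upper age limit for inclusion". Employment status is recorded at baseline (Data collection section).

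**The concern.** A participant who is not back at work at six months, or who leaves the study before returning, has no observed time. What is known is only that the time exceeds the last contact. A questionnaire score at a visit has no such feature, so the summary that suits OMAS, SEFAS and SF-36 does not suit these three outcomes.

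If those without an event are left out, the slowest recoveries are removed, and not necessarily in equal proportion in the two arms. The arms are then compared on differently selected subsets. Recovery times also tend to be skewed, which mean and SD describe poorly.

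At stake is the pilot's description of short-term effects, which is part of its stated aim. The follow-on trial is to test whether immediate weight bearing "results in improved patient reported outcomes and earlier return to work without an increase in complications", so the same summary could be carried forward. Because the protocol states the method, this is an unsuitable choice and not merely a detail left for a fuller document.

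**Working it through.** **Inputs.** From the protocol: follow-up of six months (taken as 26 weeks), 32 participants at 1:1 (16 per arm), mean and SD as the summary. The protocol gives no return rates, return times or distributions, so those below are assumptions. It has no figure for these outcomes to reproduce. Its 50 per group rests on OMAS alone (difference 10.5, SD 16, 90% power, two-sided 0.05); it reproduces (49 by the normal approximation, 50 by the t-test) and does not bear on this point.

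**Illustration with exponential times.** Let p be the proportion returned by 26 weeks.
- Mean parameter: m = −26 / ln(1 − p)
- Mean among returners only: m − 26(1 − p)/p
- Restricted mean time to 26 weeks: m × p

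| p | m | Returners only | Restricted mean |
|---|---|---|---|
| 0.90 | 11.29 | 11.29 − 26 × 0.10/0.90 = 8.40 | 11.29 × 0.90 = 10.16 |
| 0.75 | 18.76 | 18.76 − 26 × 0.25/0.75 = 10.09 | 18.76 × 0.75 = 14.07 |

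Difference between arms: restricted mean 14.07 − 10.16 = 3.9 weeks; returners only 10.09 − 8.40 = 1.7 weeks. Loss: 1 − 1.69/3.90 = about 57%.

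**Sensitivity with lognormal times.** Assumed medians, immediate/delayed, of 8/12, 6/12, 10/14 and 12/18 weeks, with the same log-SD in both arms (0.5, 0.7 or 0.9). Non-return at 26 weeks is then 0–20% (immediate) and 6–34% (delayed). The returners-only difference against the 26-week restricted mean difference:
- least affected (6/12, log-SD 0.5): 5.58 against 6.38 weeks, 13% lost;
- middle (8/12, log-SD 0.7): 2.67 against 3.82 weeks, 30% lost;
- most affected (12/18, log-SD 0.9): 1.96 against 3.51 weeks, 44% lost.

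**Patterns that go another way.**
- Inflated: immediate arm with median 8 and log-SD 1.0, delayed arm with median 12 and log-SD 0.5. Restricted means 10.63 and 13.18 (difference 2.5 weeks); returners only 8.55 and 12.34 (difference 3.8 weeks).
- Reversed: delayed arm, 70% return at mean 10 weeks and 30% do not return. Immediate arm, 70% at mean 10, 20% at mean 22 and 10% do not return. Returners only: (0.7 × 10 + 0.2 × 22)/0.9 = 12.7 against 10.0, so the immediate arm looks slower. Restricted means: 7 + 4.4 + 0.1 × 26 = 14.0 against 7 + 0.3 × 26 = 14.8, so it is in fact faster.
- Negligible: medians 3/8 weeks with log-SD 0.4. Non-return is 0.2% at most, and the difference is 5.38 weeks among returners against 5.41 restricted.

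**The case against.** The strongest reply is that this is a 32-person pilot with descriptive reporting only. These outcomes are secondary, no between-arm test is planned, and success is judged on recruitment, adherence and drop-out. The logged times stay available for reanalysis. All of that stands, and it limits the severity.

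Four stronger readings are tempting, and the document does not support them.

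- A reader might infer that mean and SD must shrink the difference. That is the expected direction if the delayed arm is simply slower, but the patterns above show inflation, reversal or no material effect. Without return rates, neither direction nor size can be known.
- A reader might put the loss in the exponential illustration at 77%, setting 1.7 weeks against the difference in full means of 18.8 − 11.3 = 7.5 weeks. That benchmark extrapolates an assumed tail beyond 26 weeks, and six-month data cannot estimate it under any method. The restricted mean is the fair comparator.
- A reader might call it an error to score non-returners at 26 weeks. With complete follow-up, that gives exactly the 26-week restricted mean, a valid summary. It fails for those who drop out earlier, and the protocol does not say which handling is meant.
- A reader might infer wrong planning values for the full trial. That trial's sample size comes from OMAS, and nowhere does the protocol use the pilot's return-to-work times for planning.

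Nor is it a flaw that people without a job have no return-to-work time. Leaving them out is the right restriction; it only needs to be stated.

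The exponential illustration also suits return to work better than time to full weight bearing, because the delayed arm is to "remain non-weight bearing for six weeks prior to allowing weight bearings as tolerated", so its times cannot start at zero.

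**Conclusion.** The point holds in a limited form. The protocol fixes a summary for fully observed data on three outcomes that are right-censored at six months or at earlier drop-out. A returners-only mean can bias the descriptive comparison. If the delayed arm is slower with a similar spread, the bias is toward zero: about 57% of the 26-week restricted mean difference in the exponential illustration, and 13% to 44% in the lognormal scenarios. All of these sizes rest on assumed distributions and return rates.

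Time to full weight bearing is probably the least affected of the three, and return to work and pre-injury activities the most; that is a judgement, as the protocol gives no rates. Severity is minor to moderate. No feasibility criterion and no sample size depends on it.

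**What to change.** For the three times, replace mean and SD by the following, by arm:
- Kaplan-Meier curves, censoring at last contact or six months, with the median and its 95% confidence interval, or the restricted mean time to 26 weeks;
- the proportion returned at six weeks, three months and six months;
- for return to work, only participants employed at injury, with that number stated.

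Say also whether return to pre-injury activities is a time, so that the Secondary outcome measures and Statistical analysis sections agree. Keep mean and SD for OMAS, SEFAS and SF-36.

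The cost is a change of wording. The logs and employment status are already collected, and SPSS, the named software, produces Kaplan-Meier estimates. The downside is wide intervals at about 16 per arm, fewer for return to work, and a median may not be reached if fewer than half return in an arm. The proportion returned remains reportable in that case.
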